### Intervention

2.5

All OFCs will be conducted in accordance with the PRACTical ALLergy (PRACTALL) guidelines (7).

Participants with IgE-mediated HEA will be randomly assigned to one of two groups: the intervention group (4-EL) or the control group (5-EL), with both protocols conducted over 6-week intervals (Table 2 and Supplementary Table S1).

**Table 2 T2:** Comparison of the 4-step (intervention) and 5-step (control) Egg ladder protocols in children with hen's Egg allergy.

Tested product (temperature, heating duration)	The amount of tested product	The amount of whole hen's egg proteins per portion [g]	The amount of hen's egg proteins per 100 g [g]	4- Step Egg Ladder (intervention group)	5- Step Egg Ladder (control group)
MUFFIN 0.75 Temp. 180°C (oven) Heating duration: 30 min (or until center is dry)	1 muffin (approx. 50 g)	0.75	1.5	–	STEP 1
6 weeks of regular dietary exposure to the tolerated quantity of the previously assessed forms					
MUFFIN 1.5 Temp. 180°C (oven) Heating duration: 30 min (or until center is dry)	1 muffin (approx. 50 g)	1.5	3	STEP 1	STEP 2
6 weeks of regular dietary exposure to the tolerated quantity of the previously assessed forms					
PANCAKE Temp. medium heat – approx. 180–190°C (frypan) Heating duration: 2–3 min both sides (until a golden-brown color is achieved)	1 pancake (approx. 84 g)	2.0	2.4	STEP 2	STEP 3
6 weeks of regular dietary exposure to the tolerated quantity of the previously assessed forms					
HARD- BOILED EGG Temp. approx. 100°C; should be added to the water once it reaches a rolling boil Heating duration: 10–12 min	1–3 years: 0.5–1 egg 4–5 years: 1 egg (approx. 50 g)	3.0 per 0.5 egg^a^ 6.0 per egg^a^	12.0	STEP 3	STEP 4
6 weeks of regular dietary exposure to the tolerated quantity of the previously assessed forms					
Almost raw egg: SOFT-BOILED EGG Temp. approx. 100°C; should be added to the water once it reaches a rolling boil Heating duration: 5 min	1–3 years: 0.5–1 egg 4–5 years: 1 egg approx. 50 g)	3.0 per 0.5 egg^a^ 6.0 per egg^a^	12.0	STEP 4	STEP 5
				Duration: 18 weeks	Duration: 24 weeks

a Amounts of hen's egg protein were estimated based on the average content in a medium egg (50 g).

The 4-EL protocol [muffin (1.5 g hen's egg proteins), pancake, hard-boiled egg, and soft-boiled egg] and the 5-EL protocol (beginning with a muffin containing 0.75 g of hen's egg proteins, followed by 1.5 g, and then the remaining steps of the 4-EL) are both based on modifications of previously published egg ladders used in clinical practice (13, 15).

Instead of using raw egg as the final step, we chose to assess tolerance to soft-boiled egg, which is considered almost raw. This decision is justified mainly by practical considerations to increase parents and child's acceptability, and to prioritize the reintroduction of foods that are more likely to be regularly consumed in everyday diets.

At each step of the ladder, a single food product was selected and applied consistently across both study arms. The quantity of hen's egg proteins at each stage was determined based on recommendations from the PRACTALL consensus report (7) and the BSACI guidelines (15).

#### Supervised oral food challenge

2.5.1

Oral food challenges at each step of the egg ladder will be conducted under hospital conditions by a research physician. Data on the hen's egg protein content in the study products (per portion and per 100 g) are presented in Table 2.

Prior to each OFC, parents will receive detailed recipes for home preparation of the products, as well as information on medications that must be discontinued before the OFC (Supplementary Material 1). OFC will be performed after a minimum four-hour fast. For younger children, a light, low-fat snack (equivalent to 0.5 of a standard portion) may be allowed two hours prior to the scheduled challenge.

In accordance with PRACTALL consensus (7) the OFC will be conducted using a four-dose challenge protocol (1/16–1/8–1/4 – and the remaining amount of a muffin), with 30-minute intervals between each administered portion of the tested product. Following the final dose, the patient will be monitored in an inpatient setting for two hours. If no adverse reaction occurs, the child may be discharged and should be closely observed at home by a parent for an additional 24 h to rule out any delayed allergic reactions.

While the double-blind, placebo-controlled food challenge is considered the gold standard for the diagnosis of HEA (15), we will conduct open-label OFCs to enhance feasibility and encourage parental cooperation. To reduce bias, we will use the predetermined stopping criteria based on objective signs.

Despite providing standardized recipes and instructing parents to strictly follow the instructions, there is still a possibility of inaccurate food preparation (e.g., baking nine muffins instead of eight). Therefore, prior to each OFC, a researcher will weigh the test product (e.g., muffin or other food item) to precisely estimate the actual amount of hen's egg proteins consumed by the child. Both the tested portion and the total amount of the prepared egg-containing food will be weighed and recorded

#### Duration of each ladder step and reintroduction of HEPs at home

2.5.2

The literature lacks a standardized egg ladder protocol, including the time intervals between its consecutive stages. Scientific societies suggest intervals ranging from 1 to 9 months (12–16). In the Canadian egg ladder protocol, a 1–3 month interval between stages is recommended (13). In this study, based on our own clinical experience, we hypothesized that a 6-week interval would be sufficient to assess the acquisition of tolerance to each subsequent stage of the egg ladder.

Following a negative OFC result and careful 24-h home observation, parents will be instructed to regularly reintroduce hen's egg proteins at home. This study follows the BSACI guidelines (15), which recommended the administration of hen's egg proteins three times per week. Over a six-week period, caregivers will introduce hen's egg proteins in the same quantity and form that did not elicit an allergic reaction during the preceding OFC.

Participants progressing to advanced EL stages will incorporate into their diet the dose of hen's egg proteins tolerated during the previous OFC, along with one to two additional portions of hen's egg proteins products from lower EL steps. The total intake should not exceed three hen's egg proteins-containing products per day. To ensure safety, home consumption of higher-step EL products is not permitted until tolerance has been confirmed through a hospital-based OFC.

Tested food products and their amount were developed according to the BSACI (15) and PRACTALL guidelines (7) and RCT by de Vlieger et al. (12) (Table 2).

#### Children with a positive OFC

2.5.3

A positive OFC is defined according to the criteria outlined in the PRACTALL guidelines (Supplementary Table S2) (7). The OFC will be stopped if any red ('Stop') criterion is met, or if two (2) orange (“Observation”) criteria are met.

In the event of a positive OFC result with baked egg (Step 1 of the EL), children will continue with an elimination diet.

A positive OFC result at later stages of the ladder will prevent progression to the next step. At home, the allergen will continue to be administered in the previously tolerated form, with dosage and frequency determined by the research team.

All children with a positive OFC will be excluded from further participation in the study and will receive continued care from the department in accordance with established clinical standards. A repeat OFC will be scheduled within 6–12 months, based on an individual risk assessment of potential adverse events and the attending physician's clinical judgment.

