### Study objective and hypothesis

2.1

The primary aim of this study is to evaluate and compare the efficacy and safety of a 4-step egg ladder (4-EL) and a 5-step egg ladder (5-EL) in children diagnosed with IgE-mediated hen's egg protein allergy.

We hypothesize that the 4-EL, with 6-week intervals, will be sufficient for assessing tolerance to hen's egg proteins in children with IgE-mediated allergy and will result in a greater proportion of children achieving tolerance to raw egg white, confirmed by OFC, compared to the 5-EL, with the same timeframe. This corresponds to an 18-week tolerance acquisition period in the 4-EL group vs. 24 weeks in the 5-EL group.

There is some evidence suggesting that the introduction of baked egg in high-risk children (e.g., those with a history of anaphylaxis) may be both safe and effective (21). However, it remains unclear whether the initial tested dose of baked hen's egg protein in such cases should be lower than, or the same as, that recommended for the general pediatric HEA population.

Therefore, we decided to compare two ladder protocols: the 4-EL, beginning with a muffin containing 1.5 g of hen's egg proteins, and the 5-EL, in which the first two steps consist of muffins containing 0.75 g and 1.5 g of egg proteins, respectively. This approach allows for a reduced allergen load at initial exposure and a longer cumulative exposure to baked hen's egg proteins. Such a strategy may be more appropriate for specific subgroups of patients, particularly those considered to be at higher risk (21).

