### Adherence

2.7

To systematically assess participant adherence and monitor the occurrence of anaphylactic events, parents will be instructed to meticulously document, on a daily basis, the quantity and frequency of at-home allergen administration during the final week preceding each OFC, as well as to record any suspected adverse reactions occurring at any time throughout the six-week interval between OFCs, using the Egg Ladder Monitoring Diary (developed by the study investigators, Additional File 2*****). This diary in paper form will be maintained throughout the six-week intervals between OFCs.

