#### Secondary outcomes

2.11.2

All secondary outcomes will be reported as a difference between two study arms.
The percentage of children with a negative OFC at each step of the EL protocol upon completion of the study's observation period (18 weeks and 24 weeks, depending on the study arm), calculated as the proportion of children tolerating the full planned dose for each step.The proportion of children who experience anaphylaxis during the observation period (18 or 24 weeks, depending on study arm), defined as reactions with severity grades 3–5 according to the updated 2023 WAO clinical criteria for anaphylaxis (27).The proportion of children with anaphylaxis (grades 3–5, per 2023 WAO criteria) who required epinephrine administration, categorized by:
○one or two doses of intramuscular epinephrine with a good clinical response (less severe reaction, grade 3),○more than 2 doses of intramuscular epinephrine,○lack of significant clinical improvement after two doses (severe reactions, grades 4–5),○measured during the observation period (18 or 24 weeks, depending on the study arm).The proportion of children who experienced systemic allergic reactions (SAR) of grades 1, 2, and 3 according to the 2023 WAO grading system, with specific reference to gastrointestinal symptoms:

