### Study discontinuation criteria

2.13

Participant withdrawal from the study may occur under the following circumstances: voluntary withdrawal of consent by one or both parents/legal guardians, any perceived risk to the child's health, non-adherence to the study protocol, loss of contact with the participant, or the formal conclusion of the study.

In the event of premature withdrawal, the investigator will ensure that all evaluable endpoints are documented in the Clinical Research Form (CRF), unless the parents/legal guardians explicitly refuse further participation. If the discontinuation of the intervention is due to a confirmed and/or potential adverse event, the child will continue to be monitored, with all relevant observations recorded in both the medical records and the CRF.

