### Harms

2.15

This study is of a cognitive-practical nature, and participants may not derive any direct clinical benefit. The proposed OFC procedures at each stage of hen's egg protein tolerance assessment are consistent with standard clinical practice. The only distinction introduced by this study is the random allocation to either an 18-week or 24-week observation arm. Outside the context of the study, the timing between OFCs would be determined solely at the discretion of the child's attending physician.

The assessment of patient and caregiver quality of life, as well as caregiver anxiety levels, requires an additional time commitment of approximately 15 min to complete standardized questionnaires designed to assess these domains.

All adverse events will be systematically documented in the Clinical Research Form (CRF) and categorized based on the International Council on Harmonization Good Clinical Practice (ICH-GCP) guidelines (32). Each event will be thoroughly evaluated to determine its duration, severity, and potential relationship with the administered intervention.

To ensure timely reporting and clinical assessment of any adverse events, participants will have access to the principal investigator via telephone and electronic mail.

In accordance with the CONSORT extension for harms reporting (33), all reported symptoms will be documented for all randomized participants, regardless of whether they complete the study. Adverse event data will be reported separately for each study arm and for each specific type of event, including the exact frequency of occurrence and distinguishing between participants with single and recurrent events.

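### After a positive OFC, Section 2.5.3 ends study participation while directed home egg can continue inside the anaphylaxis window; other sections point the other way, so capture of home reactions is unsettled

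*Protocol article*

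**What the plan says.** All references are to the protocol article.

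- Section 2.5.3, failure at the first step: "In the event of a positive OFC result with baked egg (Step 1 of the EL), children will continue with an elimination diet".
- Section 2.5.3, failure at a later step: the child does not move up. "At home, the allergen will continue to be administered in the previously tolerated form, with dosage and frequency determined by the research team".
- Section 2.5.3, study status after failure at any step: "All children with a positive OFC will be excluded from further participation in the study". Care passes to the department, and a repeat OFC follows 6 to 12 months later.
- Section 2.11.2 defines the safety outcome per child over the whole window: "The proportion of children who experience anaphylaxis during the observation period (18 or 24 weeks, depending on study arm").
- Section 2.7, on the Egg Ladder Monitoring Diary, where parents record suspected home reactions: "This diary in paper form will be maintained throughout the six-week intervals between OFCs".
- Section 2.13, where the intervention stops because of a confirmed or potential adverse event: "the child will continue to be monitored, with all relevant observations recorded in both the medical records and the CRF".
- Section 2.14 treats a reaction during an OFC as an adverse event, has the challenge stopped, and then lets the spacing of later ladder steps be set individually.
- Section 2.15: "all reported symptoms will be documented for all randomized participants, regardless of whether they complete the study".
- Section 2.19 plans an intention-to-treat analysis of all randomised children.

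**The concern.** A child who reacts at the pancake, for example, goes on eating a lower-step egg product at home on the research team's instruction, inside the period over which anaphylaxis is counted. Under 2.5.3 that child has already left the study. The intention-to-treat denominator keeps the child, but the planned way of collecting home reactions depends on a next study OFC that will not take place.

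Sections 2.13 and 2.15 suggest that collection continues, and 2.14 suggests that the ladder itself may continue. A site that follows 2.5.3 and a site that follows 2.13 to 2.15 would collect different safety data for the same child. Safety is named with efficacy in the primary aim (Section 2.1), although anaphylaxis itself is a secondary outcome. The time affected can also differ by arm, because the same 1.5 g muffin is Step 1 in one ladder and Step 2 in the other.

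**Working it through.** **Inputs.** Steps are 6 weeks apart (Section 2.5, Table 2), so OFC k falls at week 6 × (k − 1). The 4-EL has S = 4 steps and the 5-EL has S = 5. Recruitment is 47 per arm (Section 2.9).

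**The plan's own figures.** Window length is 6 × (S − 1): 6 × 3 = 18 and 6 × 4 = 24 weeks, which matches "18-week tolerance acquisition period in the 4-EL group vs. 24 weeks in the 5-EL group". Recruitment: 42 / 0.9 = 46.7, rounded up to 47 per arm. Both reproduce.

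**Weeks of home egg left in the window after a positive OFC.** This is 6 × (S − k), set to zero at Step 1 because the child goes on elimination.

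| Food failed | 4-EL | 5-EL |
|---|---|---|
| Muffin 0.75 g | not used | Step 1: 0 |
| Muffin 1.5 g | Step 1: 0 | Step 2: 6 × 3 = 18 |
| Pancake | Step 2: 6 × 2 = 12 | Step 3: 6 × 2 = 12 |
| Hard-boiled egg | Step 3: 6 × 1 = 6 | Step 4: 6 × 1 = 6 |
| Soft-boiled egg | Step 4: 0 | Step 5: 0 |

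The repeat OFC comes at 6 months (about 26 weeks) at the earliest. That is beyond the longest remaining period of 18 weeks, so it closes no diary interval within the window. The 6-week follow-up in Section 2.8 is for children who have completed the ladder.

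**Size of the time at risk.** The protocol gives no step failure rates, so these are assumptions. Let a be the proportion failing 0.75 g, b the proportion failing 1.5 g after tolerating 0.75 g, and c the proportion failing at each of pancake and hard-boiled egg. With the same thresholds in both arms:

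- 4-EL child-weeks = 47 × (1 − a)(1 − b) × [12c + 6c(1 − c)]
- 5-EL child-weeks = the same expression with its own c, plus 47 × (1 − a) × b × 18

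For a = b = 8% and c = 5%, the proportion failing at 1.5 g is 1 − 0.92² = 15.4%. This lies within the 3–30% implied by the 70–97% baked-egg tolerance in the Introduction. Then:

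- 4-EL: 47 × 0.8464 × (0.60 + 0.285) = 35.2 child-weeks, in 3.9 children.
- 5-EL: 35.2 + 47 × 0.92 × 0.08 × 18 = 35.2 + 62.3 = 97.5 child-weeks, in 7.3 children.
- Planned child-weeks are 47 × 18 = 846 and 47 × 24 = 1,128.

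| a | b | c in 4-EL | c in 5-EL | 4-EL weeks | 5-EL weeks |
|---|---|---|---|---|---|
| 8% | 8% | 5% | 5% | 35.2 | 97.5 |
| 10% | 10% | 10% | 10% | 66.2 | 142.4 |
| 10% | 2% | 10% | 10% | 72.1 | 87.4 |
| 10% | 0% | 10% | 10% | 73.6 | 73.6 |
| 10% | 5% | 20% | 10% | 135.0 | 108.0 |
| 10% | 2% | 20% | 10% | 139.3 | 87.4 |

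When later failure rates are equal, the whole arm difference is the single term in b. It vanishes at b = 0. In the last two rows, where the longer ladder is assumed to halve later failures, the order reverses.

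**From time to events.** No home anaphylaxis rate is given. At an assumed 1 per 1,000 child-weeks, the first row corresponds to about 0.04 and 0.10 events; at 1 per 100, to about 0.4 and 1.0.

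**The case against.** The strongest reply is that exclusion in 2.5.3 means leaving the ladder, with harms still collected. Section 2.15 has adverse events recorded in the CRF, covers non-completers expressly, and gives families telephone and e-mail access to the principal investigator. Section 2.13 continues monitoring when an adverse event ends the intervention, and 2.14 treats an OFC reaction as one. The children stay in the department's care. An adverse event protocol and the diary itself are mentioned but not shown, and may hold the detail. The diary is therefore not the only route by which a home reaction could reach the trial.

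Much of this stands, and it rules out saying that reactions are certainly lost. It does not settle the matter. Section 2.15 covers symptoms that are reported, which is passive collection. Section 2.13 does not name a positive OFC and gives neither an instrument nor an end date. Section 2.14 can be squared with 2.5.3 only if a stopped OFC is not always a positive one. An unseen document may add detail, but it does not remove an explicit exclusion sentence in this one.

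Two further replies also stand. The home food is the form the child tolerated, not the one that caused the reaction. And because the outcome counts each child once, a child whose positive OFC was itself anaphylaxis is already counted. Only children with a non-anaphylactic positive OFC can be missed, so missed events may be few.

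**Conclusion.** The point holds as an internal contradiction with a real consequence for outcome ascertainment. Section 2.5.3 ends participation while directed home exposure can continue for up to 12 weeks (4-EL) or 18 weeks (5-EL) of the anaphylaxis window. Sections 2.7, 2.13, 2.14 and 2.15 do not agree on what is collected in that time. If 2.5.3 is followed, active capture stops and home reactions may go unrecorded.

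A reader might infer that such reactions are missed as a matter of fact. The documents do not support that, because 2.13 and 2.15 point to continued recording. A reader might also infer that more are missed in the 5-EL, so that the comparison is biased against the 4-EL. The schedule makes a difference possible through the 1.5 g muffin, but its size and direction depend on failure rates in each arm and on home reaction rates, none of which the protocol gives. The illustrative child-weeks run from 35 against 97 to 139 against 87.

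**What to change.** In Section 2.5.3, replace the exclusion sentence with a statement that a child with a positive OFC stops the ladder and counts as not tolerant for the primary outcome, but stays in the study for safety data to the end of the assigned 18- or 24-week window. The home-reaction diary continues over that time, and one contact at the end of the window records any reaction. Amend 2.7 so that the diary is not tied to a next OFC, and reconcile 2.13, 2.14 and 2.15 with the new text, including whether 2.14 allows further steps after an OFC reaction.

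Nothing here changes what the child eats at home or how a reaction is managed. The cost is an amendment to these sections, additional diary sheets, and one contact for each affected child: about 4 in the 4-EL and 7 in the 5-EL under the first set of assumptions above, and more if step failures are commoner.

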#### Assessments

2.6.2

Anthropometric data for the child, specifically height and weight, will be collected at study enrollment and at the end of the observation period (either at 18 or 24 weeks, depending on the assigned study arm). Weight (in kilograms) and standing height (in centimeters) will be measured according to standardized protocols.

Prior to the initial OFC and following completion of the egg ladder, the subjective quality of life of all enrolled children and their caregivers will be assessed using the validated, allergy-specific Parent Form of the Food Allergy Quality of Life Questionnaire (FAQLQ-PF) (24). The FAQLQ-PF was developed to measure parental perceptions of health-related quality of life in children aged 0–12 years with food allergies and includes three domains: emotional impact, food anxiety, and social and dietary limitations. In this study, only the age-appropriate versions of the questionnaire for children under 4 years and for those aged 4–6 years will be used, in accordance with the inclusion criteria. These versions contain 14 and 26 items, respectively. A total score ranging from 0 to 6 is calculated as the mean of the subscale scores.

Prior to each OFC, caregivers will assess their level of anxiety specifically related to the OFC using the Subjective Units of Distress Scale (SUDS) (25). On this scale, parents will rate their anxiety from 1 to 100, where 0 represents no anxiety or complete relaxation, and 100 represents extreme anxiety – the highest level of distress ever experienced.

In children with atopic dermatitis, objective skin lesions will be evaluated using the objective SCORAD index (oSCORAD) (26), a validated variant of the Severity Scoring of Atopic Dermatitis (SCORAD). Assessment will be performed prior to the initial OFC and during follow-up examinations at the end of each observation period.

The SCORAD index is a key tool for evaluating the severity of atopic dermatitis and monitoring treatment response It includes both objective measures (extent and intensity of skin lesions), and subjective symptoms (pruritus and sleep disturbance) reported over the preceding 72 h. The oSCORAD omits the subjective component, focusing exclusively on objective clinical findings. The maximum oSCORAD score is 83, with an optional addition of up to 10 points for disfiguring or function-limiting changes in severe cases. Severity categories are defined as follows: mild (<15), moderate (15–40), and severe (>40).

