#### Primary outcome

2.11.1

The primary outcome is the percentage of children who acquire tolerance to soft-boiled hen's egg (almost raw hen's egg proteins), as determined by a negative OFC at the final step of the EL. Soft-boiled egg will be administered at the end of the observation period (18 or 24 weeks, depending on the assigned study arm).

The challenge dose will consist of 0.5–1 egg for children aged 1–3 years and 1 egg for those aged 4–5 years, corresponding to a maximum total of 6 g of hen's egg proteins. The outcome will be reported as a difference between two study arms.

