### Statistical analysis

2.19

Descriptive statistics will be used to summarize baseline characteristics. For continuous variables, comparisons between groups will be made using the Student's *t*-test, Mann–Whitney *U*-test or Wilcoxon signed rank test, depending on whether or not the variables are normally distributed. The appropriate statistical test will be employed to compare percentages, either the χ^2^ test or Fisher's exact test.

For continuous outcomes, the differences in means or medians (depending on the distribution of data), and for dichotomous outcomes, the relative risk (RR) and number needed to treat (NNT), all accompanied by a 95% CI, will be calculated. The difference between study groups will be considered statistically significant if the *p*-value is less than 0.05, if the 95% CI for RR does not include 1.0, or if the 95% CI for mean difference does not include 0. All statistical tests will be two-tailed and performed at the 5% level of significance.

An intention-to-treat (ITT) analysis including all randomised participants, regardless of protocol adherence or withdrawal, will be applied. A per-protocol analysis that includes all participants who finish the study according to the protocol will also be performed.

The number of missing data with reasons will be reported for each study arm, and compared qualitatively between groups, if feasible. Multiple imputation methods for missing data will be applied to address missing data, as recommended (34).

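### Children with a positive OFC before the last step have no final OFC and are not explicitly scored, so known failures can be left out of the per-protocol rate or imputed in the ITT rate

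*Protocol article*

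**What the plan says.** Section 2.5.3 sets two rules for a positive oral food challenge (OFC). On progression: "A positive OFC result at later stages of the ladder will prevent progression to the next step". On participation: "All children with a positive OFC will be excluded from further participation in the study".

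Section 2.11.1 defines the primary outcome as tolerance to soft-boiled egg at the last step of the ladder. On timing it says: "Soft-boiled egg will be administered at the end of the observation period (18 or 24 weeks, depending on the assigned study arm"). The result is read "as determined by a negative OFC at the final step of the EL".

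Section 2.19 has three relevant sentences:
- On the main analysis set: "An intention-to-treat (ITT) analysis including all randomised participants, regardless of protocol adherence or withdrawal, will be applied".
- On absent values: "Multiple imputation methods for missing data will be applied to address missing data, as recommended".
- On the second analysis set: "A per-protocol analysis that includes all participants who finish the study according to the protocol will also be performed".

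Section 2.6.2 plans the FAQLQ-PF questionnaire for these times and children: "Prior to the initial OFC and following completion of the egg ladder, the subjective quality of life of all enrolled children". It covers the caregivers as well. Weight and height are taken at enrolment and at the end of observation.

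No sentence scores a child stopped by an earlier positive OFC as not tolerant. None says whether that child's unperformed final OFC is missing data, or whether the child has finished according to the protocol.

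**The concern.** A positive OFC before the last step is a known failure to reach the primary outcome. The protocol takes that child out of the study, defines the outcome by a test the child will not have, builds one analysis set from those who finish, and imputes what is missing. Each rule is ordinary alone. Together they allow an analysis in which known failures are left out or given an imputed result.

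The resulting rate would describe children who climbed the ladder as far as the last step, not the children randomised. The two ladders differ in their early steps (first muffin 1.5 g in 4-EL, 0.75 g in 5-EL), so early failure is where an arm effect may appear. Section 2.17 makes the trial fully unblinded. With two readings available, the choice could be made after the data are seen.

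The exclusion also stops data collection. Children who fail early are out of the study before the end-of-observation FAQLQ-PF and growth measures, while ITT is promised for all randomised participants.

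**Working it through.** **The plan's own figure.** Section 2.9 gives 84 completers and 10% dropout: 84/(1 − 0.10) = 93.3, rounded up to 94; per group 42/0.90 = 46.7, rounded up to 47. This reproduces. No power-based sample size is stated.

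**Who is affected.**
- Positive at the final step: the primary outcome is observed. Nothing is imputed, and the child has finished.
- Negative at every step: observed and tolerant.
- Positive before the final step: the failure is recorded, but there is no final OFC. Only this group is unclassified.

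**Effect on one arm's rate.** Let p be the share of randomised children tolerant at the final step, and f the share of failures that occur before the final OFC. The completer rate is p / [p + (1 − p)(1 − f)]. Take p = 0.69 from the meta-analysis cited in the Introduction. The documents do not give f, so it is varied:
- f = 0: 69%
- f = 0.25: 0.69/0.9225 = 74.8%
- f = 0.50: 0.69/0.845 = 81.7%
- f = 0.75: 0.69/0.7675 = 89.9%
- f = 1: 100%

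As a cross-check, assume equal pass rates at every step. The final-step pass rate is then 0.69^(1/4) = 91% in 4-EL and 0.69^(1/5) = 93% in 5-EL.

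**Imputation.** Every child with an observed final OFC passed all earlier steps. Imputation under missing-at-random that ignores OFC history would therefore give roughly the completer rate. Adding OFC history as a predictor does not help by itself, because no child with an earlier positive OFC has an observed final result to learn from. The sIgE, tIgE and BAT values taken before each OFC (section 2.6.3) could soften this, to an unknown degree.

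**Effect on the arm difference.** For illustration, use 80% (4-EL) and 69% (5-EL), the rates the Introduction reports for an earlier egg trial. The true difference is 11 points. Among completers it becomes:
- f = 0.50 in both arms: 88.9% − 81.7% = 7.2 points
- f = 0.75 in both arms: 94.1% − 89.9% = 4.2 points
- f = 0.50 in 4-EL, 0.75 in 5-EL: 88.9% − 89.9% = −1.0 point

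With an equal true rate of 69% in both arms, f = 0.50 against 0.75 alone produces 81.7% − 89.9% = −8.2 points. Swapping the two shares gives +8.2. With f = 0.75 against 0.80 it is 89.9% − 91.8% = −1.9 points.

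**Effect on completers.** If early failures count as non-completers, with p = 0.69 and no other dropout, 94 recruited leave 94 × 0.845 = 79 (f = 0.50) or 94 × 0.7675 = 72 (f = 0.75), against the stated minimum of 84.

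**If early failures are scored as not tolerant.** The denominator stays at 47 per group. At 80% against 69% the expected counts are 37.6 and 32.4, the difference is 11 points and the relative risk is 0.80/0.69 = 1.16, whatever f is.

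**The case against.** The strongest reply is that the protocol already gives the right answer. The primary outcome counts children with a negative final OFC, and ITT keeps every randomised child in the denominator. A child who never has a negative final OFC is then simply not tolerant. Stopping at a positive OFC is also what the protocol prescribes, so such a child may be said to have finished according to it. This reading is legitimate, and it means that a reader who infers that the plan does drop or impute these children goes further than the text. It is not the only reading, however. A child excluded from the study has, in plain words, not finished it, and the imputation sentence makes no exception.

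A second reply is that scoring and the imputation model belong in an analysis plan that is not shown. For scoring, that plan could settle the matter. But the exclusion and the per-protocol definition based on finishing are stated here, and no analysis plan can recover assessments that were never made.

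A third reply is that withdrawal and harms are covered. Section 2.13 has evaluable endpoints recorded at premature withdrawal and monitoring continued after an adverse event, and section 2.15 has symptoms reported for all randomised children. This stands for harms. It does not secure FAQLQ-PF and growth at 18 or 24 weeks in children whose participation ended earlier.

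**Conclusion.** The point holds as an ambiguity with material consequences, not as a stated error. Sections 2.5.3, 2.11.1 and 2.19, applied literally, allow failures before the last step to be left out of the per-protocol rate and imputed in the ITT rate. At a true 69%, this would raise an arm's rate to between 75% and 90% for f from 0.25 to 0.75. Both the 69% and the range of f are illustrative.

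The arm difference is distorted when f differs between arms. That is plausible, since 5-EL has one more OFC before the last step and a lower first dose, but the documents fix neither the direction nor the size. Under equal pass rates per step the two arms' final-step pass rates differ by only about 2 points (91% and 93%). A reader might infer that the trial's result would reverse. That needs assumed inputs that the documents do not supply.

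A reader might also infer that all later data on these children are lost. Harms are covered. The gap is FAQLQ-PF and growth at the end of observation.

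**What to change.** In sections 2.11.1 and 2.19, state that:
- a positive OFC at any step is an observed non-tolerant result in every analysis and is never imputed;
- multiple imputation of the primary outcome applies only to children lost without a positive OFC;
- the per-protocol set keeps children who stopped because of a positive OFC.

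In section 2.5.3, replace exclusion from the study by a statement that these children stop ladder progression but remain in study follow-up for the already planned end-of-observation FAQLQ-PF and growth measures.

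Reconcile section 2.5.3 with section 2.13 (monitoring after discontinuation for an adverse event) and section 2.14 (the interval to subsequent steps set individually after an adverse event in an OFC). This is a matter of consistency and requires no change to any clinical rule.

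The cost is wording plus one assessment per affected child, and section 2.5.3 already keeps these children under the department's care. The recruitment target of 94 is unchanged.
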